### Aim 1: target engagement (analyzed as single-group)

Across doses, we will test whether decreases in within-DMN (mPFC-PCC) functional connectivity occur (during MRI Session 2) from pre- to post-mbNF. MPFC-PCC functional connectivity estimates for each rsfMRI run (including pre-mbNF runs) will be treated as the outcome variable in linear mixed-effects models, with time (0 = pre-mbNF, 1 = post-mbNF) as the focal predictor, such that there will be 4 observations (2 pre-mbNF and 2 post-mbNF runs) for each participant with complete data:$$DMN\_connectivity \sim time + framewise\_displacement + age + (time | id)$$

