In summary, the current randomized clinical trial (RCT) (ClinicalTrials.gov Identifier #NCT05617495; R61MH132072) will enroll depressed adolescents ages 13–18-years-old. Participants will be randomized to either a 15-min or 30-min dose of mindfulness-based neurofeedback (mbNF) and clinical assessments will be completed over a one-month follow-up. The following hypotheses will be tested. First, a single session of mbNF will lead to reductions in within-DMN functional connectivity *(Aim 1: Target Engagement)*. Second, a 30-min session will lead to greater reduction in within-DMN functional connectivity compared to the 15-min session *(Aim 2: Dosing Impact on Target Engagement)*. As all participants will receive an active mbNF intervention, the current study is regarded as open-label. Aim 1 analyses will treat the study as a single-group trial, and analyses for aim 2 will leverage randomization to treat the study as a parallel-group superiority trial.

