### Statistical analyses

Quality control checks will be conducted for data of all modalities before analysis, including inspection of missing data, examining ranges and distributions, and checking modeling assumptions. Analyses will include age (years) as a covariate. Analyses of fMRI data will also include covariates for head motion in each run (mean Jenkinson Framewise Displacement).

Analyses will be conducted using the intention-to-treat principle, such that all available data from all participants *randomized* to receive 15-min versus 30-min of mbNF will be analyzed [102]. Specifically, all available data passing quality control checks will be analyzed from participants who were randomized to a dose condition at the MRI visit, whether or not participants complete the intended duration of mbNF. Although we anticipate that the majority of participants will complete all study procedures, attrition and missing data (i.e. failing MRI quality assurance) will be reported. Imputation will be conducted at the item level for incomplete self-report measures with < 10% of items missing, though missing data for fMRI or fully missing self-report outcome measures will not be imputed.

Linear mixed-effects models using all available data will be used to test all primary hypotheses using the lme4 package [103] with the most up-to-date version of the R statistical software [104]. For all tests, we will report 95% CI and use 2-sided *p*-values with alpha level of 0.05 for significance. Robust estimation will be conducted if outliers ≥ 3 standard deviations from the mean are identified for outcome variables, and Bayesian estimation via the brms package will be used if frequentist analyses exhibit numerical problems resulting in convergence issues [105]. All models will include random intercepts, and for each analysis separately, model comparison (using the AIC metric, or PSIS-LOO for Bayesian models) will determine whether models will also include random slopes (as indicated in the model syntax below; see https://github.com/pab2163/mindful_brain_project/tree/main/materials for full notation) for each participant (Table 2).

**Table 2 Tab2:** Primary and secondary analysis hypotheses, outcomes, and methods

Aim	Hypothesis	Outcome Measure	Analysis Method	Term of Interest

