### Aim 2: Dosing Impact on Target Engagement (Analyzed as parallel-group)

We will test dosing effects of mbNF (15-min versus 30-min condition) on change in mPFC-PCC connectivity (during MRI Session 2) from pre- to post-mbNF. Models will be similar to Aim 1, with an added time (0 = pre-mbNF, 1 = post-mbNF) x dose (15-min versus 30-min condition) interaction term to test differential effects of dosing on pre-post change as follows:$$DMN\_connectivity \sim dose*time + framewise\_displacement + age + (time | id)$$

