### Secondary analyses

#### Clinical outcomes (analyzed as single-group)

Across doses, analyses will explore changes in clinical outcomes from pre- to post-mbNF. Analyses will examine changes from baseline to the 1-month follow-up in depression symptoms using the self-reports (MFQ) and interviewer assessments (CDRS-R), as well as self-reported rumination using the RRS. Sum scores will be used as outcome measures for the MFQ and RRS. Further analyses will explore changes in EMA reports of depressive symptoms (sum of PHQ-2 EMA items) and rumination (sum of RRS & PTQ EMA items). Change will be examined from pre-mbNF to both the week immediately after and the week of the 1-month follow-up. Clinical outcomes will each be analyzed similarly to primary analyses using linear mixed-effects regression models as follows:$$clinical\_measure \sim time + age + (time | id)$$

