### Power calculation

G*power was used to estimate required sample sizes [119]. For Aim 1, achieving 80% power will require an estimated 76 participants (allowing ~ 15% data loss from *N* = 90) to detect significant (*p* < 0.05) within-participant change of small-medium effect sizes (f > 0.19), assuming sphericity and *r* > 0.3 between repeated measures. For Aim 2, achieving 80% power will require 38 participants in each dosing group (allowing ~ 15% data loss from *N* = 45 per group) to detect *p* < 0.05 significant dosing group x time interactions of medium effect sizes (f > 0.25), assuming sphericity and *r* > 0.3 between repeated measures.

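### The Aim 1 and single-group clinical models leave out the randomised dose; if dose matters, the interval for the average change is modestly too wide and its target is not fixed

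*Protocol article*

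**What the plan says.** The Introduction declares the pooling: "Aim 1 analyses will treat the study as a single-group trial". The Aim 1 section repeats it, "Across doses, we will test whether decreases in within-DMN (mPFC-PCC) functional connectivity occur (during MRI Session 2) from pre- to post-mbNF", and gives a mixed model with time, framewise displacement and age as fixed effects and a participant intercept and slope. Dose does not appear. The Aim 2 section uses the same outcome and adds dose and a dose-by-time "interaction term to test differential effects of dosing on pre-post change".

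The clinical outcomes follow the same pattern. The single-group section says "Across doses, analyses will explore changes in clinical outcomes from pre- to post-mbNF" and fits time and age only; the section after it fits dose by time.

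Table 2 lists the main effect of time and the time-by-dose interaction as the terms of interest. It lists no change within an arm. The Sensitivity analyses section adds site, sex, mindfulness experience and service use as covariates, but not dose. The Statistical analyses section lets AIC decide, for each analysis separately, whether the random slope stays.

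**The concern.** The plan's second primary hypothesis is that the 30-min arm changes more than the 15-min arm. If so, a model without dose treats a known, balanced, designed difference as unexplained variation between people. Under 1:1 allocation that difference adds nothing to the sampling variance of the average change, so the reported standard error is larger than the true one. The better Aim 2 holds, the less efficient the Aim 1 test becomes.

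Two further matters follow. Without dose in the model, the average is weighted by however many usable post-mbNF scans each arm supplies, so its target is not fixed in advance. And Aim 1 is worded as the effect of a single session of mbNF although it averages two sessions of different length, in a trial that means to identify the better dose.

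**Working it through.** **Inputs (Power calculation; Statistical analyses).** Tests: "use 2-sided *p*-values with alpha level of 0.05 for significance". Aim 1: "achieving 80% power will require an estimated 76 participants (allowing ~ 15% data loss from *N* = 90"), for "within-participant change of small-medium effect sizes (f > 0.19), assuming sphericity and *r* > 0.3 between repeated measures". Aim 2: "achieving 80% power will require 38 participants in each dosing group", with f = 0.25 and the same correlation. Allocation is 1:1 (Abstract).

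**Reproducing the Aim 1 figure.** With one pre and one post measure, the standardised change is 2f/√(2(1 − r)) = 0.38/√1.4 = 0.321 SD of change. With 76 participants the noncentrality is 0.321 × √76 = 2.80 and power is 78.9%, close to the stated 80%.

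**Interval width.** Let d be the between-arm difference in mean change, in within-arm SDs of change: d = 4f/√(2(1 − r)). Leaving dose out at 1:1 turns the variance of change from 1 into 1 + d²/4, while the true sampling SD of the average stays at 1/√76 = 0.115. Approximate power without dose is Φ(2.80 − 1.992·√(1 + d²/4)). The last three columns take the average change as 0.321 SD.

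| Interaction f | d | Variance | SE ratio | Aim 1 power without dose | 15-min change | 30-min change |
|---|---|---|---|---|---|---|
| 0.10 | 0.338 | 1.029 | 1.014 | 78.2% | 0.15 | 0.49 |
| 0.19 | 0.642 | 1.103 | 1.050 | 76.0% | 0.00 | 0.64 |
| 0.25 | 0.845 | 1.179 | 1.086 | 73.8% | −0.10 | 0.74 |

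With dose in the model, power is 78.9% in every row. In interval width, f = 0.25 amounts to 76/1.179 = 64.5 participants, a loss of about 12. At d = 0.655, close to the smallest difference detectable with 80% power at 38 per arm, it is 76/1.107 = 68.6, a loss of about 7.

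**The plan's four runs.** A mixed-model simulation with two pre and two post runs and the random slope kept gave width ratios of 1.09 to 1.17 at a between-arm difference of 1 SD of the outcome, and 1.01 to 1.05 at 0.4 SD. With the slope left out while true slopes varied, coverage of the pooled interval fell to 89% to 93%: too narrow, not too wide. When true slopes varied, AIC kept the slope in at least 81% of simulated trials.

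**Unequal loss (rates assumed; the document gives none by arm).** If w is the 30-min share of usable participants, the pooled estimate departs from the equal-weight average by (w − 0.5)d.
- 15% loss in both arms: w = 0.5, shift 0.
- 10% loss (15-min) and 20% (30-min): w = 0.8/1.7 = 0.471. The shift is −0.010 SD at f = 0.10 and −0.025 SD at f = 0.25, or 0.09 to 0.22 standard errors.
- 0% and 30%: w = 0.7/1.7 = 0.412. The shift is −0.030 to −0.075 SD, or 0.26 to 0.65 standard errors.

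**No change in the 15-min arm (20,000 simulated trials per row, 38 per arm).**

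| Interaction f | Pooled Aim 1 positive | Aim 2 significant | Aim 1 positive, Aim 2 not |
|---|---|---|---|
| 0.10 | 30% | 31% | 21% |
| 0.15 | 56% | 59% | 24% |
| 0.19 | 76% | 79% | 17% |
| 0.25 | 93% | 95% | 4% |

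**The case against.** The pooling is a declared choice. The Abstract, Introduction, Table 2 and the analysis sections all say that Aim 1 is single-group, and averaging over two active doses is a legitimate target. The widening is small and errs on the safe side. These points stand, and they limit this to an improvement.

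Three stronger readings are tempting, and the document does not support them.

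- **A reader might infer that Aim 1 has less power than the protocol states.** That holds only if f = 0.19 is standardised by the within-arm SD of change. If it refers to the pooled SD, any dose heterogeneity is already inside it and the stated power stands; including dose would then be a gain in efficiency. Judged by power alone, the loss is also smaller than the width figures suggest: 73.8% power corresponds to about 67 participants, a loss of about 9 of 76.
- **A reader might infer that the plan would hide a 15-min arm with no change.** The planned dose-by-time models test the difference directly, and with 15 min as the reference level their time coefficient is that arm's change. At f = 0.25 a positive Aim 1 with a non-significant Aim 2 occurs in only 4% of trials. The Introduction also reports that the pilot found reduced connectivity after a 15-min session. What stands is that the plan does not commit to showing each arm's change, and that at f = 0.10 to 0.19 the misleading combination occurs in 17% to 24% of trials if the 15-min arm does not change.
- **A reader might infer a known attrition bias.** No loss by arm is given. The shift is a bias only against an equal-weight average, which the plan never names, and it moves the estimate by a fraction of a standard error. Attrition will be reported and analyses for data missing not at random are planned. Unequal loss is plausible, since the 30-min arm has six more 3-min runs (18 minutes) before the post-mbNF resting scans, but it is not shown.

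**Conclusion.** The omission is real: the Aim 1 and single-group clinical models lack the randomised factor, and no sensitivity analysis supplies it. If dose matters and the random slope is kept, the interval for the average change is about 1% too wide at f = 0.10, 5% at 0.19 and 9% at 0.25. With the planning effect taken in within-arm SDs, Aim 1 power at f = 0.25 is about 74% against 79%. The direction is conservative. It can reverse if AIC drops the random slope while true slopes vary, so the width claim is conditional on that step. Unequal loss would move the estimate away from an equal-weight average, by 0.65 standard errors or less over the assumed range. A positive pooled result should not be read as an effect of each dose, above all when Aim 2 is non-significant. None of this makes Aim 1 as planned invalid.

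**What to change.** Fit one model for both primary aims: `DMN_connectivity ~ time*dose_c + framewise_displacement + age + (time | id)`, with `dose_c` = −0.5 for 15 min and +0.5 for 30 min. Take Aim 1 from the time coefficient and state that it is the equal-weight average of the two doses. Take Aim 2 from the interaction. From the same fit, report each arm's pre-post change with its 95% CI, and base any statement about one dose on that dose's own interval. Make the same change to the single-group clinical models and the matching rows of Table 2.

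The cost is a formula line, a few words and one degree of freedom for the change (75 to 74), with no extra participants, scans or visits. With no dose effect, simulated Aim 1 power was 0.791 with or without the dose terms.

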### Aim 2: Dosing Impact on Target Engagement (Analyzed as parallel-group)

We will test dosing effects of mbNF (15-min versus 30-min condition) on change in mPFC-PCC connectivity (during MRI Session 2) from pre- to post-mbNF. Models will be similar to Aim 1, with an added time (0 = pre-mbNF, 1 = post-mbNF) x dose (15-min versus 30-min condition) interaction term to test differential effects of dosing on pre-post change as follows:$$DMN\_connectivity \sim dose*time + framewise\_displacement + age + (time | id)$$

### Secondary analyses

#### Clinical outcomes (analyzed as single-group)

Across doses, analyses will explore changes in clinical outcomes from pre- to post-mbNF. Analyses will examine changes from baseline to the 1-month follow-up in depression symptoms using the self-reports (MFQ) and interviewer assessments (CDRS-R), as well as self-reported rumination using the RRS. Sum scores will be used as outcome measures for the MFQ and RRS. Further analyses will explore changes in EMA reports of depressive symptoms (sum of PHQ-2 EMA items) and rumination (sum of RRS & PTQ EMA items). Change will be examined from pre-mbNF to both the week immediately after and the week of the 1-month follow-up. Clinical outcomes will each be analyzed similarly to primary analyses using linear mixed-effects regression models as follows:$$clinical\_measure \sim time + age + (time | id)$$

#### Dosing Impact on Clinical Outcomes (Analyzed as parallel-group)

Secondary analyses will also test dosing effects of mbNF (15-min versus 30-min condition) on change in clinical outcomes from pre- to post-mbNF as follows:

$$clinical\_measure \sim dose*time + age + (time | id)$$

Secondary analyses each involve tests of 7 outcome measures (EMA reports of depression (1) and rumination (2) the week following mbNF; EMA reports of depression (3) and rumination (4) the week of the 1-month follow-up, and CDRS-R (5), MFQ (6), and RRS brooding subscale (7) at 1-month follow-up. For EMA analyses, participants with ≥ 5 responses will be included. Given 4 tests for depression symptom outcomes and 3 tests for rumination outcomes for secondary analyses respectively, the Benjamini–Hochberg procedure will be used to control the false discovery rate at an alpha level of 0.05 [115].

### Exploratory analyses

#### Within-DMN connectivity

In addition to mPFC-PCC connectivity, we will also test connectivity change between a larger set of DMN nodes including mPFC, PCC, subgenual anterior cingulate cortex, angular gyrus, and lateral temporal cortex. We anticipate reduced functional connectivity among distributed nodes within the DMN beyond mPFC and PCC.

#### Default mode network and frontoparietal network functional connectivity

In parallel analyses to Primary Aims 1 and 2, we will test changes in functional connectivity between the DMN and FPN from pre-post mbNF, as well as dosing impacts. We anticipate stronger negative correlations (anti-correlations) between DMN-FPN post-mbNF.

#### Acceptability of mbNF

Analyses will also examine in-scanner and post-mbNF ratings of participants’ experience with mbNF to assess acceptability and adherence.

### Power calculation

G*power was used to estimate required sample sizes [119]. For Aim 1, achieving 80% power will require an estimated 76 participants (allowing ~ 15% data loss from *N* = 90) to detect significant (*p* < 0.05) within-participant change of small-medium effect sizes (f > 0.19), assuming sphericity and *r* > 0.3 between repeated measures. For Aim 2, achieving 80% power will require 38 participants in each dosing group (allowing ~ 15% data loss from *N* = 45 per group) to detect *p* < 0.05 significant dosing group x time interactions of medium effect sizes (f > 0.25), assuming sphericity and *r* > 0.3 between repeated measures.

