**Methods:**

Adolescents (*N* = 90) with a current diagnosis of MDD ages 13–18-years-old will be randomized in a parallel group, two-arm, superiority trial to receive either 15 or 30 min of mbNF with a 1:1 allocation ratio. Real-time neurofeedback based on activation of the frontoparietal network (FPN) relative to the DMN will be displayed to participants via the movement of a ball on a computer screen while participants practice mindfulness in the scanner. We hypothesize that within-DMN (medial prefrontal cortex [mPFC] with posterior cingulate cortex [PCC]) functional connectivity will be reduced following mbNF *(Aim 1: Target Engagement).* Additionally, we hypothesize that participants in the 30-min mbNF condition will show greater reductions in within-DMN functional connectivity *(Aim 2: Dosing Impact on Target Engagement).* Aim 1 will analyze data from all participants as a single-group, and Aim 2 will leverage the randomized assignment to analyze data as a parallel-group trial. Secondary analyses will probe changes in depressive symptoms and rumination.

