**Discussion:**

Results of this study will determine whether mbNF reduces functional connectivity within the DMN among adolescents with MDD, and critically, will identify the optimal dosing with respect to DMN modulation as well as reduction in depressive symptoms and rumination.

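### The Aim 2 power statement does not follow from its own inputs: at f = 0.25 and r = 0.3, 38 per group gives about 95% power, not 80%

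*Protocol article*

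**What the plan says.** The Power calculation section reports that "G*power was used to estimate required sample sizes". For Aim 2 it states "For Aim 2, achieving 80% power will require 38 participants in each dosing group", after allowing about 15% data loss from 45 per group. The target is "dosing group x time interactions of medium effect sizes (f > 0.25), assuming sphericity", with a correlation above 0.3 between repeated measures. For Aim 1, the same section gives 76 participants, 80% power, f > 0.19 and the same correlation.

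Other inputs stand elsewhere in the article. The Statistical analyses section says the trial will "use 2-sided *p*-values with alpha level of 0.05 for significance". The abstract gives the allocation: participants "receive either 15 or 30 min of mbNF with a 1:1 allocation ratio". The Aim 2 section defines the tested term as the interaction of two-level time (pre, post) with two-level dose.

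The article does not state how many measurements per participant were entered in G*Power or which effect-size option was chosen. It does not express f as a difference in connectivity.

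**The concern.** Aims 1 and 2 are planned with the same total (76), correlation, alpha and power, yet the article gives them different detectable effects, f = 0.19 and f = 0.25. With two time points, G*Power uses the same noncentrality formula for the within-participant time effect and for the group-by-time interaction, and the error degrees of freedom differ by one (75 and 74). The two detectable f values should therefore be practically equal, so at least one of the two statements cannot be right.

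Aim 2 is the only randomised comparison and a primary aim. Its power statement is what a reader will use to judge how informative the dose comparison can be, so power, f and n should agree with one another.

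**Working it through.** **Inputs.** Two-sided alpha 0.05 (Statistical analyses). f = 0.25, r = 0.3, sphericity and 38 per group, so N = 76 (Power calculation). 1:1 allocation (abstract). k = 2 groups and m = 2 time levels (Aim 2 section). The values of f and r are given as lower bounds and are used at those bounds. That m = 2 was entered in G*Power is an inference, checked in step 1.

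**Formula** (G*Power repeated-measures ANOVA, default effect-size option). Noncentrality λ = f² × N × m / (1 − r). For the interaction, df1 = (k − 1)(m − 1) and df2 = (N − k)(m − 1).

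**1. Check the convention on Aim 1.** For one group, f = 0.19 and N = 76: λ = 0.0361 × 76 × 2 / 0.7 = 7.84 on F(1, 75), and power is 78.9%. At f = 0.193 power is 80%. The stated f > 0.19 with 76 participants is therefore reproduced to within rounding of f. With m = 4, Aim 1 power would be 92.4%, so m = 2 is the setting that fits.

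**2. Apply the same convention to Aim 2.** λ = 0.0625 × 76 × 2 / 0.7 = 13.57 on F(1, 74), and power is **95.3%**. A simulation of 20,000 trials, analysed by a t test on change scores, gave 95.3%. A normal approximation gave 95.8%.

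**3. N needed at f = 0.25, r = 0.3, balanced groups.**

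| Target power | Total N | Per group |
|---|---|---|
| 80% | 46 | 23 |
| 90% | 62 | 31 |
| 95% | 76 | 38 |

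N = 74 gives 94.8%, so 76 is the smallest balanced total that reaches 95%.

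**4. Effect detectable with 80% power at 38 per group.** Solving for f gives 0.193 (λ = 8.06).

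**5. Other settings that might give 80% at f = 0.25 and N = 76** (r = 0.3 unless stated).

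| Setting | Power |
|---|---|
| Interaction, m = 4 | 99.6% |
| Interaction, r = 0 | 86.0% |
| Interaction, r = 0.5 | 99.0% |
| Interaction, alpha 0.01 | 84.7% |
| Cohen effect-size option | 57.6% |
| SPSS effect-size option | 56.5% |
| Between-group main effect, m = 2 / 3 / 4 | 76.1% / 83.8% / 87.7% |
| Interaction, 38 read as the total N | 71.7% |

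None comes within two percentage points of 80%. The interaction formula would need r = −0.18.

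**6. f in plain units.** In a 2 × 2 interaction, cell effects of ±f SD make the dose groups differ in pre-post change by 4f SD. Here SD is that of a single pre or post measurement, with one measurement per time point. The change-score SD is √(2 × (1 − 0.3)) = 1.183 of those units.

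- f = 0.193: 4 × 0.193 = 0.77 SD, or 0.77 / 1.183 = 0.65 change-score SD.
- f = 0.25: 4 × 0.25 = 1.0 SD, or 1.0 / 1.183 = 0.85 change-score SD.

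**7. Allowance for the planned model.** Aims 1 and 2 use two runs per time point. If r = 0.3 holds between all runs, the SD of the change in two-run means is √0.7 = 0.837 run-level SD. The 80% detectable difference is then 0.651 × 0.837 = about 0.54 run-level SD.

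**The case against.** The strongest reply is that the error does no harm. At the stated f and r the trial has more power than claimed. No sample size, error rate or analysis depends on the sentence, and f = 0.25 carries the conventional label of medium. All of this stands, and it sets the weight of the point.

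It can also be said that the G*Power settings are not given, so the calculation cannot be called wrong with certainty. This stands in part. However, the setting that reproduces Aim 1 gives 95% for Aim 2, and none of the alternatives tried restores 80%. Larger f or r only raises power further.

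A reader might go further and infer that the dose comparison is underpowered, that a null interaction is likely, or that power is only about 15%. The documents do not support this. The article gives no expected dose effect and no dose-response shape. The Aim 1 value of f is an effect detectable with 80% power, not a forecast. The 15% figure needs an assumed doubling of effect from 15 to 30 minutes, and it also ignores the second run at each time point.

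Nor does the correction make detectability less favourable: the 80% detectable f falls from 0.25 to 0.19.

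A reader might also want the abstract's statement that the trial "critically, will identify the optimal dosing with respect to DMN modulation" reworded. That is a separate matter. The article already defines Aim 2 as a superiority test and commits to 95% confidence intervals, and it nowhere says that a non-significant interaction would show 15 minutes to be enough.

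**Conclusion.** The Aim 2 sentence is wrong as written. With two groups, two time points, r = 0.3, two-sided alpha 0.05 and 38 per group, power at f = 0.25 is about 95%, against the stated 80%. The 80% detectable effect is f of about 0.19, equal to that of Aim 1. That 76 is exactly the total for 95% power suggests a 95% calculation reported as 80%, but this is an inference from the match.

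The result rests on the default G*Power effect-size option and m = 2, neither of which the article states. The error is conservative and touches neither enrolment nor the analysis, so this is a minor correction of a stated figure. The SD equivalents hold for one measurement per time point and need that qualification wherever they are quoted.

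**What to change.** Replace the Aim 2 sentence with wording such as: *With 38 per group, r = 0.3 and two time points, power is 80% for f = 0.19 and 95% for f = 0.25.* Then:

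- State the number of measurements and the G*Power effect-size option used, for both aims.
- Give the equivalent difference between doses in pre-post change: about 0.77 SD at f = 0.19 and 1.0 SD at f = 0.25 (0.65 and 0.85 change-score SD). Define SD as that of a single pre or post measurement, with one measurement per time point.
- Add that averaging two runs per time point would lower the 80% detectable difference to about 0.54 run-level SD, if r = 0.3 holds between all runs.

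The cost is wording only. The allowance for data loss (45 to 38 per group) and the enrolment target stay as they are.
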